### Study Phase 2: Cross-sectional Survey of SCA Users and SCA Nonusers

#### Structure

A survey will be used in a case-control design. The questionnaire was piloted with 5 participants and will take approximately 15-25 minutes for participants to complete. The survey will comprise different evaluated scales (for further details, see Multimedia Appendix 1) and sociodemographic variables as well as specific questions to the usage of SCAs. This study phase will be conducted and reported according to the STROBE statement [30]. Owing to the limited amount of literature on SCA users and nonusers, pilot interviews with 2 SCA users and 1 SCA expert will be conducted to ensure a meaningful concept selection for the survey. Simultaneously, concepts will be derived from existing literature that is connected to the use of health apps and could reveal the potential characteristics of the user group such as eHealth Literacy [36], personality [37,38], hypochondria [39], self-efficacy [40,41], and need for cognition [42]. Affinity for technology [43], satisfaction with the GP [44], and overall life satisfaction [45] will also be considered. Moreover, we will assess the perceived usefulness of SCAs and requirements for SCAs in open-ended questions of the survey since this might be a central aspect of acceptance of SCAs as the Technology Acceptance Model (TAM) induces. The TAM was already introduced by Davis [46] in 1989 and is based on the theory of reasonable action and the theory of planned behavior. The TAM (and its further expansions) is still one of the most prevailing models to examine factors affecting a users’ acceptance of new technologies [47]. The model assumes a mediating function of perceived ease of use and usefulness in association with system characteristics and system usage [47].

#### Sample and Recruitment

The sampling process was conducted from November 2020 until the end of June 2021. A case-control design using 2 recruitment strands is planned. An a priori power analysis using PASS 2020 (v20.0.3, NCSS) revealed a sample size of 375 (β=.8, α=.05, nuisance parameter=0.2; n_user_=188, n_nonuser_=188) for an odds ratio of 2.5. The targeted odds ratio corresponds to a small-to-medium effect of Cohen *d* [48] and was selected because we consider that this will be an effect size that contributes a meaningful explanation of variance in the logistic regression. As this study has an explorative character, we could not derive theory-driven assumptions for a multivariate logistic regression. Hence, we based the power analysis on a univariate logistic regression. We will use a univariate logistic regression to identify meaningful predictors for the usage of SCAs and will moreover set up a multivariate model that includes all the identified predictors. Our multivariate model will be the first proposal and will need further research to confirm the univariate predictors in a multivariate model.

The sample will be composed of different recruiting strands to achieve a representative sample. In the first strand, German citizens will be contacted via mail to participate in the survey. The intended recipients will be representatively selected by an external partner (T + R Dialog Marketing and Acxiom). Further participants will be recruited via mailing lists of the University of Tübingen and the University Hospital of Tübingen, social media, and cooperating GP practices. After 3 months, the representativity of this sample will be checked. If the return rate is too low or if certain groups are not sufficiently represented, there will be additional recruiting via the proposed channels.

The second strand of the sampling process aims to integrate symptom checker users only. We expect only a small number of symptom checker users. To ensure a sample size of n_user_=188, a targeted recruitment via social media advertisements and the social media channels of the University Hospital of Tübingen will be conducted.

Inclusion criteria in general are the ability to give consent and German language skills of at least B1 of the Common European Framework of References for Languages. Participants of the second recruitment strand can only be included if they have experience with SCAs.

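### The Phase 2 sample-size line states 20% power (β=.8), and its printed inputs do not lead to the printed total of 375

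*Protocol article*

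**What the plan says.** In the Protocol article, Study Phase 2, Sample and Recruitment, an a priori calculation in PASS 2020 "revealed a sample size of 375", with the settings, the split and the target effect given as "β=.8, α=.05, nuisance parameter=0.2; n_user_=188, n_nonuser_=188) for an odds ratio of 2.5". The same paragraph says that the calculation was based on a univariate logistic regression. It does not say what the nuisance parameter is, whether the test is one- or two-sided, or what share of participants is assumed to carry the predictor. The figure for users then serves as a recruitment target: "To ensure a sample size of n_user_=188", a second recruitment strand through social media was planned.

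**The concern.** Two things in this line do not hold together.

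- **The power is misstated.** β conventionally denotes the type II error, so β=.8 is a power of 0.20. No other sentence in the article gives the power, so nothing corrects it.
- **The inputs do not produce the result.** Reading β=.8 as power 0.80 and the 0.2 as a baseline probability, the required total is half of what is printed.

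This line is the only justification for the target of 188 users. As it stands, a reader cannot tell what power the comparison of users and nonusers was planned to have, or how small an odds ratio it could be expected to detect.

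**Working it through.** **Inputs from the article:** odds ratio (OR) 2.5, α=.05, β=.8, nuisance parameter 0.2, 188 users and 188 nonusers, total 375, univariate logistic regression.

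**Assumptions needed because the article is silent:** 0.2 is the baseline (reference-group) probability; the test is two-sided; power 0.80 was meant.

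**1. Attempt to reproduce 375**

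Second probability: p1 = 2.5×0.2 / (1 − 0.2 + 2.5×0.2) = 0.5/1.3 = 0.3846. Mean: (0.2 + 0.3846)/2 = 0.2923.

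n per group = [z(α/2)·√(2·p̄·(1−p̄)) + z(power)·√(p0(1−p0) + p1(1−p1))]² / (p1−p0)²

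- First term: 1.960 × √(2×0.2069) = 1.2607
- Second term: 0.8416 × √0.3967 = 0.5301
- (1.2607 + 0.5301)² / 0.1846² = 3.207/0.03408 = 94.1 per group, or **188.2 in total**

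The sample-size formula for logistic regression with one binary predictor, half of the sample exposed, also gives 188.2. The printed 375 is not reproduced.

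**2. The same reading with β=.8 taken literally**

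At 20% power, z(power) = −0.8416, and (1.2607 − 0.5301)²/0.03408 = 15.7. Rounded up, this is 16 per group or **32 in total**. So 20% power cannot be what was planned.

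**3. What 188 per group delivers on this reading**

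Power for OR 2.5: Φ[(0.1846×√188 − 1.2607)/√0.3967] = **0.978**. The OR detectable with 80% power is **1.94**. Both are for one unadjusted test at α=.05.

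**4. Other readings (power 0.80)**

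| Reading | Required |
|---|---|
| Baseline 0.2, two-sided, continuity correction | 210 in total |
| Baseline 0.2, two-sided, Wald on log OR | 196 in total |
| Baseline 0.2, one-sided | 148 in total |
| 0.2 as exposure share, half users, two-sided | about 261–276 in total |
| 0.2 as share of discordant pairs, two-sided | 211 pairs (exact test about 225) |
| 0.2 as share of discordant pairs, one-sided | 166 pairs (approximate formula) |

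None of these gives 375.

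**5. Settings that do come near 375 (two-sided)**

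- Baseline 0.10, 25% exposed, no R²: 374.6
- R²=0.2 with other covariates, baseline 0.10, half exposed: 377.2
- Baseline 0.2 with an exposure share of roughly 13% or 85%: 375

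Each needs a value that the article does not print. An R² with other covariates also has no role in a model with one predictor.

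**6. Internal sum**

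188 + 188 = 376, against 375 printed. Half of 375 is 187.5, so rounding each group up would explain the difference.

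**The case against.** The strongest counter-argument is that β=.8 is an obvious slip for power .80 that changed no design decision, and that an incompletely described calculation is not a wrong one. The 0.2, the sidedness and the exposure share are undefined. With one added input a univariate logistic regression does return 375, even with 0.2 as the baseline. A condensed article may also leave software settings to a fuller document.

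Much of this stands. The slip is very likely one of notation, and 375 is not shown to be wrong under every PASS procedure. It does not remove the point, because the article chose to print inputs and a result: the power is printed wrongly, and the result does not follow from the inputs given.

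A reader might be tempted by stronger conclusions that the document does not support:

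- **That 94 per group is the right size.** This depends on the assumed meaning of 0.2, a two-sided test and, in the logistic version, a half-exposed sample.
- **That a total was mistaken for a group size and doubled.** The match of 188.2 with 188 is suggestive. But doubling 188 gives 376, and halving 375 and rounding up gives 188, so the printed figures fit equally well with a program output of 375 that was then split.
- **That the target is slightly too small.** If 0.2 is the discordant share in the planned matching, 188 pairs have about 77% power (71% with the exact test), but only for a two-sided test. A one-sided exact test gives 81.6%.
- **That the effect is mislabelled.** "The targeted odds ratio corresponds to a small-to-medium effect of Cohen"'s d is the article's description. The usual conversion, ln(2.5)×√3/π = 0.505, lies at the conventional medium mark, so the label is at most imprecise.

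**Conclusion.** The line is wrong as written on power: it states 20% where 80% was almost certainly intended, and nothing in the article corrects it. Its printed inputs also do not yield 375. On the natural reading they yield about 188 in total, half the printed figure; 375 appears only once an unprinted input is supplied.

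The 188, the 98% power and the detectable OR of 1.94 rest on 0.2 being the baseline probability, equal groups, a two-sided test and a single unadjusted comparison at α=.05. The article plans a correction for multiple testing, which would lower that power.

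On this reading the discrepancy is conservative, so it does not show the study to be underpowered. The Results section reports data collection finished with n=1074, without a count of users, so the consequence lies in how the planned power and detectable effect are reported, not in recruitment.

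**What to change.** - Write power = 0.80 (β = 0.20).
- State what the 0.2 is, whether the test is one- or two-sided, the assumed exposure share, and which PASS procedure was used.
- Rerun the calculation. Then either show the full inputs that give 375, or keep 188 per group and state its actual power and detectable OR. If 0.2 is the baseline and the test is two-sided, these are about 98% for OR 2.5, and OR 1.94 at 80% power.
- Reconcile 375 with 188 + 188 = 376, for example by saying that each half was rounded up, if that is so.

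The cost is one rerun of the power calculation and a reworded paragraph, which can be carried into the survey's results paper. No change to the collected data is needed.

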#### Analysis

The level of use for SCAs, awareness of SCAs, and general interest in SCAs will be described using the first recruitment strand with descriptive statistics.

Following the case-control design, SCA users from the first and second recruiting strand will be matched with nonusers (matched controls) from the first recruitment strand. Significant predictors will be extracted with a logistic regression. A correction for multiple testing will be applied. The recent versions of SPSS (IBM) and R statistic (R Core Team) will be used for the analyses.

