#### Focus 2: SCA Epidemiology, Users, Nonusers, and Predictors of Use

Our results will contribute to describing the user group and nonuser group of SCAs in more detail. The degree of use of SCAs in Germany will be derived, and predictors for SCA use will be identified. Moreover, vulnerable groups that might be disadvantaged through the implementation of SCAs will be described.

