### Study Course

Four main data sources will be considered, each representing a specific stakeholder group of SCAs: representative sample of the German population (divided into SCA user and nonuser), GP, and health care experts. We define SCA users as participants that have used SCAs at least once, and nonusers are participants who never used SCAs. Data collection and analysis methods will comprise qualitative and quantitative approaches.

The different methods are applied to the data sources in 4 interconnected study phases, each representing one of the four main foci of interest of the study: a literature review (study phase 1, lead: Institute of Ethics and History of Medicine, University Tübingen [IEHM], Institute of Applied Social Science, University of Applied Science Würzburg-Schweinfurt), a representative survey of SCA user and SCA nonuser (study phase 2, lead: Institute of General Practice and Interprofessional Care, University Hospital Tübingen [IGP]), an SCA user diary-based self-observation combined with individual semistructured interviews (study phase 3, lead: IEHM), and lastly, single semistructured interviews with GPs and health care experts (study phase 4, lead: Institute of Occupational and Social Medicine and Health Services Research, University Hospital Tübingen [IOSM] for GP interviews, lead: IGP for health care experts interviews). For this study protocol, we will follow the Good Reporting of A Mixed Methods Study (GRAMMS) [27] checklist. Preferred Reporting Items for Systematic reviews and Meta-Analyses extension for Scoping Reviews (PRISMA-ScR) [28,29], STROBE (STrengthening the Reporting of OBservational studies in Epidemiology) [30], SRQR (Standards for Reporting Qualitative Research) [31], and GRAMMS [28] checklists will be applied during the project process. The PRISMA-ScR, STROBE, and SRQR guidelines will be applied on specific study phases. The GRAMMS [28] guideline will be used in the context of mixed methods approaches and in the integration of results. In the following sections, the 4 study phases and their connections are described in detail.

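### Level of SCA use in Germany is taken from a first strand that pools a population-selected mailing with convenience channels, so the figure depends on the channel mix and is open to selection bias of unknown size and direction

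*Protocol article*

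**What the plan says.** - **Target.** Focus 2 under Objectives sets a population quantity: "The degree of use of SCAs in Germany will be derived". Study Course supplies the definition: "We define SCA users as participants that have used SCAs at least once". Principal Findings lists degree of use in Germany among the main outputs.
- **Data source.** Study Phase 2, Analysis, says that level of use, awareness and general interest "will be described using the first recruitment strand with descriptive statistics".
- **What the first strand contains.** Study Phase 2, Sample and Recruitment, starts with a mailing: "The intended recipients will be representatively selected by an external partner". It then adds, with no condition attached: "Further participants will be recruited via mailing lists of the University of Tübingen and the University Hospital of Tübingen, social media, and cooperating GP practices".
- **Safeguard.** "After 3 months, the representativity of this sample will be checked". The stated response to a poor return, and likewise to gaps in the make-up of the sample, is a top-up: "if certain groups are not sufficiently represented, there will be additional recruiting via the proposed channels".
- **Second strand.** Only people with SCA experience can enter it. They are sought by targeted recruitment on social media, and the level-of-use description does not draw on this strand.
- **Status claimed.** Study Course calls the population sample representative. Strengths and Limitations relies on the survey's representativeness to set the qualitative results in a wider context.

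**The concern.** Only the mailing involves any selection intended to mirror the population. People reached through university and hospital lists, social media or a cooperating practice enter because they are connected to that channel and chose to respond. The article itself expects eHealth literacy and affinity for technology to be possible characteristics of users (Study Phase 2, Structure). Channels that plausibly select on such traits could therefore shift the use rate.

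A prevalence is directly exposed to who is in its denominator. The top-up rule can bring age or sex groups into line while leaving, within each group, people who differ from the population in digital habits or interest in the topic. A larger sample from the same channels does not reduce that error. At stake is whether a figure reported as use in Germany describes Germany or the recruitment mix.

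**Working it through.** The article gives no expected prevalence, precision target or sample size for this estimate, so there is no stated figure to reproduce. The power calculation (375 participants, odds ratio 2.5) concerns the user/nonuser regression and does not bear on it.

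**Inputs from the article**
- Achieved survey sample: 1074 in total (Results, Study Phase 2), not split by strand or channel. This is the largest that the first strand could be.
- Users are expected to be few, but no rate is given.

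**Inputs assumed, because the article gives none**
- True use rate π: 5%, with 10% as a second case.
- Share w of the first strand from convenience channels: 0.10 to 0.60.
- Ratio r of use in those channels to use in the population: 0.5 to 3.
- Mailed respondents are taken to have rate π, which isolates the channel effect and sets nonresponse aside.

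**Formulas**
- Expected pooled rate = (1 − w)π + w·r·π
- Bias = w(r − 1)π
- 95% sampling half-width = 1.96·√(π(1 − π)/n)

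**Results at π = 5%**

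| w | r | Pooled rate | Bias (points) |
|---|---|---|---|
| 0.60 | 0.5 | 3.5% | −1.5 |
| 0.10 | 0.5 | 4.75% | −0.25 |
| 0.10 | 1.5 | 5.25% | +0.25 |
| 0.25 | 2 | 6.25% | +1.25 |
| 0.50 | 3 | 10.0% | +5.0 |
| 0.60 | 3 | 11.0% | +6.0 |

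Half-width at n = 1074: 1.96·√(0.05·0.95/1074) = 0.013, or 1.3 points. Upward bias exceeds this once w(r − 1) is above 0.013/0.05 = 0.26, for example a 26% convenience share at twice the population rate, or 13% at three times.

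**Results at π = 10%.** (w, r) = (0.10, 1.5), (0.25, 2) and (0.50, 3) give 10.5%, 12.5% and 20.0%. The half-width is 1.96·√(0.10·0.90/1074) = 0.018, or 1.8 points.

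**Effect of using the mailing alone.** Setting w = 0 makes the channel term w(r − 1)π zero. Nonresponse bias within the mailing is untouched. No corrected prevalence can be computed, because neither the channel split nor any use rate is given.

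**The case against.** Several points can fairly be made for the plan.

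- **The estimator is not fixed.** The article says only descriptive statistics. A reader might infer that the figure will be unweighted, or that an interval ignoring selection will be attached to it. Neither is stated, and a fuller plan may weight or tabulate by channel. This stands. What the article does fix is the data source, the first strand as a whole, and the point rests on that. Demographic weights applied to the pooled strand would not remove selection on interest or digital habit.
- **There are safeguards.** The users-only second strand is kept out of the level-of-use description, which removes the most direct selection on the outcome, and representativity is checked after 3 months. Both deserve credit. But the only stated response to a failed check is more recruiting through the listed channels.
- **Social media serves both strands, so a reader might infer that the first strand was selected on SCA use and that the prevalence must come out too high.** The article does not support that. Second-strand recruitment is targeted and requires SCA experience, whereas the first strand has no such criterion. GP practices could push the figure either way.
- **The further channels could be read as a contingency.** The sentence carries no condition. Even on that reading, their recruits would join the first strand and be described with it.
- **The mailing is not clean either.** The plan itself anticipates that the return rate may be too low, and topic-interested people may be more likely to reply. This stands and limits what the remedy can claim.
- **The study is exploratory.** Its main modelling concerns predictors of use, which this point leaves alone. That lowers the severity, but degree of use in Germany is still a stated aim.

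**Conclusion.** The point holds as a matter of design. Following the plan as written pools convenience recruits into an estimate presented as SCA use in Germany, and the representativity check does not cure this. The result depends on the channel mix and is open to selection bias.

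The documents do not show how large that bias is or which way it goes. Over the assumed range at a 5% true rate it runs from about −1.5 to +6 points, against 1.3 points of sampling error at n=1074. That is from negligible to more than four times the sampling half-width (6/1.3 ≈ 4.6). The range rests wholly on assumed shares, ratios and true rate. It shows what is possible and is not an estimate of the error in this survey. A flat statement that the prevalence is inflated would go further than the article allows.

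The severity is should-fix: a descriptive but headline output, correctable at the analysis stage.

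**What to change.** Data collection is finished, so the change lies in analysis and reporting.

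1. Take the primary estimates of level of use, awareness and interest from the mailed respondents only, weighted to population margins (such as age, sex, education and region), with 95% confidence intervals and the mail response rate.
2. Report university and hospital list, social media and GP-practice respondents separately, as convenience samples. Give the pooled first-strand figure only as secondary.
3. State that nonresponse bias in the mailing remains after weighting, and qualify the word representative accordingly wherever it is applied to the survey.
4. This depends on recruitment channel having been recorded, which the article does not say. If it was not, qualify or withdraw the claim to describe use in Germany.

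**Cost.** A change of analysis wording and a source of population margins. The price is precision. If the first strand were the full 1074, a convenience share of 10% would leave about 967 mailed respondents and a half-width of 1.96·√(0.05·0.95/967) = 1.4 points at 5% use. A share of 60% would leave about 430 and a half-width of 1.96·√(0.05·0.95/430) = 2.1 points. Weighting would usually widen these somewhat. The user/nonuser comparison need not change.

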### Study Phase 3: Diary-Based Self-observation Combined With Semistructured User Interviews

#### Structure

Study phase 3 investigates SCA users and their usage patterns and effects of SCAs on individuals. A specific SCA (Ada app) was chosen by the study team as an example since it is considered one of the most prevalent SCAs in Germany. Following web-based training, participants will engage in a diary-based self-observation. During the observation time of 6 weeks, participants will document their daily usage and nonusage of the Ada app. Next, individual semistructured user interviews are performed with the diary study participants. The interviews allow participants to reflect on values, concepts, and knowledge gaps. This allows a supplemental exploration of the experiences recorded in the diaries. The user interviews in this study part will be conducted and reported according to SRQR statement [31].

